#### 2.3.2. Exclusion Criteria

The data of those patients who have had to apply another therapy (pharmacological, surgical, or rehabilitative) during the care provided by the physiotherapist in their usual clinical practice will not be included. For ethical reasons, this will not be explicitly explained to the families who agree to participate in this study, so as not to influence possible therapeutic decisions in the following two months. Data of the children will be followed up and can be excluded later if there is a change in their diagnosis and cerebral palsy is not confirmed at the appropriate age. The previous therapeutic trajectory, as well as concomitant treatment (such as pharmacological treatment for spasticity, dystonia, epilepsy, etc., as well as other rehabilitation interventions) was not considered within the exclusion criteria for two reasons: their effect would already be included within the rate of motor development before VT, and also because all the children were compared only to themselves. These will be noted and considered during the calculations, but the data exclusion will only occur if there are changes in them (both adding or withdrawal) during our 2 months of intervention. 

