### Statistical Methods

Statistical analysis will be performed using the SPSS 27.0 statistical software for Windows (SPSS Inc., Chicago, IL, USA; version 27.0). The normality of the sample will be checked using the Shapiro–Wilk test, and if it follows a normal distribution, an analysis of variance (ANOVA) of repeated measures p will be used, with time (pre-treatment and post-treatment) as an intra-group factor, and Vojta and conventional physiotherapy groups as the inter-group factor, all with a Bonferroni correction. Statistical analysis will be performed with a confidence level of 95%, so a *p*-value of <0.05 will be considered significant.

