## 4. Discussion and Ethical–Legal Aspects

Completed assessment data of four subjects has been collected to date, as two subjects withdrew prematurely or did not sign the consent form. Recruitment is currently ongoing at our first site and no results report is available due to the small sample. 

The baseline scoring of GMFM at initial assessment is related to the age of the child in order to understand the rate of items acquisition so far. The aim of this study is not to compare absolute values of GMFM between different subjects according to their age and, therefore, if the children are born preterm, the chronological age is considered. This allows us to plot changes due to spontaneous and therapeutic gross motor experience after birth. 

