The rate values are calculated by dividing the total score by the time (days of age) required to achieve it, assuming that the neonatal GMFM would be zero. The acceleration factor is calculated by dividing the differences between final and initial rate (assumed to be zero at birth), by the age in days (elapsed time). The same rate and acceleration factors of acquisition are figured out between the initial assessment and after two months of the intervention. Only new points acquired during this period were considered to calculate the rate of development and acceleration values in the intervention period. Because the distribution of the item acquisition during the pre-intervention period is unknown, we performed a second rate calculation assuming that all the items were adquired during the last two months before the intervention (for children older than 2 months at initial assessment). This simulation of the maximal possible pre-intervention rate and acceleration will limit the possibility of being overcome by the post-treatment values and will avoid average values slowing down the last two preintervention months. Completing all the items in the previous two months is unlikely and would make it more difficult to obtain improvements after the intervention, especially for the older children. Even if these calculations do not benefit our results, they will ensure that the rate and acceleration post-intervention can be compared within same-lasting and following periods. We know that the GMFM item acquisition is not linear, and both calculations will help us to understand if the rate differences are due to natural acceleration or a significant therapeutic change. On the other hand, this will avoid comparing low average rate values due to longer pre-intervention periods and, therefore, random positive outcomes. Rate values within each GMFM dimension will then be considered and will help to clarify the results. 

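### Using chronological age for preterm children lowers their age-based pre-treatment rate but not their treatment-period rate, which inflates the pre-post effect; the arm comparison is affected only if prematurity differs between arms

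*Protocol article*

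**What the plan says.** Section 2.6 divides the initial GMFM and IMP scores by age in months. Section 4 does the same for the GMFM in days, "dividing the total score by the time (days of age) required to achieve it, assuming that the neonatal GMFM would be zero". The pre-treatment acceleration is that rate divided by age again. For the treatment period, Section 4 counts only the points gained between the two assessments, which Section 3 sets two months apart (±1 week).

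For preterm children, Section 4 states: "if the children are born preterm, the chronological age is considered". It gives two grounds. One is: "The aim of this study is not to compare absolute values of GMFM between different subjects according to their age". The other is: "This allows us to plot changes due to spontaneous and therapeutic gross motor experience after birth".

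Section 4 adds a second pre-treatment rate. It treats the whole initial score as gained in the two months before treatment, for children older than 2 months.

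On comparisons, Section 2.3.2 says that "all the children were compared only to themselves". Statistical Methods plans a repeated-measures ANOVA with time as the within-child factor and "Vojta and conventional physiotherapy groups as the inter-group factor". Section 2.3 assigns children according to therapists' free treatment times. The variable list in Section 2.5 has age but not gestational age.

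**The concern.** The pre-treatment and treatment-period rates rest on different clocks. The pre-treatment denominator is all time since birth; for a preterm child that includes weeks before term-equivalent age, when few items are likely to be gained. The treatment-period denominator is about two months for every child. Chronological age can therefore lower only the pre-treatment value, so the age-based pre-post gain of a preterm child moves in one direction.

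That gain is used for inference: time is a factor in the ANOVA, and Section 3 says the short window is what lets changes be credited to reflex locomotion. Section 4 itself warns that long pre-intervention periods pull the average rate down and can produce chance positive findings. Chronological age lengthens that period for preterm children.

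The arm comparison is exposed in a second, conditional way. If one arm happens to hold more preterm children, or younger ones, it shows the larger artificial gain.

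**Working it through.** The protocol gives no figure on prematurity, so there is none to reproduce. Weeks early, preterm shares and variances below are assumptions; 30 per group and the 0–36 month age range are the protocol's.

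**Step 1: size within a child.** Let S be the initial score, A the chronological age and g the time born early, in months: g = weeks × 7/30.44. Eight weeks gives g = 1.84 and 12 weeks gives g = 2.76. Assume acquisition starts at term-equivalent age.

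- Planned pre-treatment rate: S/A. With corrected age: S/(A − g). Understatement = g/A.
- Planned pre-treatment acceleration: S/A². Understatement = 1 − ((A − g)/A)².
- Post/pre ratio for a child progressing at a constant rate since term age, with no treatment effect: A/(A − g).

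| Age A | Rate too low, 8 / 12 weeks early | Acceleration too low, 8 / 12 weeks | Post/pre ratio, 8 / 12 weeks |
|---|---|---|---|
| 6 months | 31% / 46% | 52% / 71% | 1.44 / 1.85 |
| 12 months | 15% / 23% | 28% / 41% | 1.18 / 1.30 |
| 24 months | 8% / 12% | 15% / 22% | 1.08 / 1.13 |
| 36 months | 5% / 8% | 10% / 15% | 1.05 / 1.08 |

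Example: 1.84/6 = 0.307, and 6/(6 − 1.84) = 1.44.

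**Step 2: what reaches the arm comparison.** The bias in the arm-by-time contrast, as a fraction of the mean rate, is about (mean of g/A among preterm children) × (difference in preterm share between arms). It is zero if the shares, and the ages of preterm children, are equal.

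**Step 3: simulation with no effect.** The set-up was 30 per arm, 20,000 runs, no treatment effect and no natural acceleration. Ages were uniform, the true rate had a coefficient of variation of 0.3, and the treatment-period rate had added noise with SD 0.3 (in units of the mean rate). The arm test was a t test on rate change, which equals the time-by-group test with two time points.

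| Ages, weeks early | False positives, pooled time effect (40%/40% preterm) | Time × group, 40%/40% | 50%/30% | 60%/20% |
|---|---|---|---|---|
| 4–12 months, 8 | 64.5% | 5.0% | 8.9% | 21.5% |
| 4–12 months, 12 | 89.1% | 5.0% | 12.1% | 36.0% |
| 4–36 months, 8 | 23.0% | 5.2% | 6.0% | 9.2% |
| 4–36 months, 12 | 42.2% | 4.9% | 7.0% | 14.3% |

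With corrected age, both tests return to about 5% in every row.

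**Step 4: the second pre-treatment rate.** This is S divided by two months. Age does not enter, so the choice of age has no effect on it. Where corrected age exceeds 2 months it is stricter than the corrected-age rate: at 6 months and 12 weeks early, S/2 against S/3.24.

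**The case against.** The strongest reply is that the protocol already has a safeguard. The two-month rate ignores age and works against finding an acceleration, so the plan as a whole is not slanted one way. That stands, and it limits the point to the age-based rate. It does not remove it. The two-month rate is restricted to children older than 2 months, its premise is one the protocol itself calls unlikely, and it is described for the GMFM and not for the IMP, the only blinded outcome. The article also gives no rule on which calculation decides.

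Second, a reader might infer that the arm comparison is biased simply because the ANOVA compares arms. The documents do not support that. The understatement arises within each child whether or not arms are compared, and comparing arms cancels it when prematurity is balanced: the time-by-group test stays near 5%.

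Third, a reader might take Section 4 to say that children are never compared with each other. It rules out only comparing absolute GMFM values by age, and an ANOVA on rates does not contradict that. The wording that conflicts with the inter-group factor is in Section 2.3.2.

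Fourth, counting from birth is deliberate. That is a legitimate definition of a rate, but it does not put the pre-treatment and treatment-period values on the same footing.

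Finally, gestational age may be part of the Phase 1 medical data in the full protocol, so its absence from Section 2.5 is weak evidence that it is not collected.

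**Conclusion.** The point holds for the age-based rate and acceleration. Relative to corrected age, the pre-treatment rate of children born 8–12 weeks early is 31–46% too low at 6 months, falling to 5–8% at 36 months. The pre-post time effect can therefore look significant with no treatment effect, in 23–89% of simulated trials with 40% preterm children in each arm.

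The arm-by-time contrast is biased only under imbalance. False positives were 6–12% with preterm shares of 50%/30% and 9–36% with 60%/20%. Allocation by therapist availability leaves such imbalance possible; nothing in the document shows that it will occur.

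All of this rests on acquisition starting near term-equivalent age and on assumed prematurity, ages and variances. The problem is a repairable analysis choice that matters most in young preterm children.

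**What to change.** - Record gestational age at birth with the Phase 1 medical data.
- Pre-state a sensitivity analysis that recomputes the age-based GMFM and IMP rates with corrected age. Limit it to children whose corrected age is clearly above zero, for example at least 2 months. Corrected age should not simply replace chronological age throughout: eligibility starts at 0 months, and at 3 months and 12 weeks early the corrected age is 3 − 2.76 = 0.24 months, so the rate is multiplied by 3/0.24 = 12.5; nearer term age the denominator reaches zero or turns negative.
- Add gestational age or preterm status as a covariate in the arm comparison.
- Base the treatment conclusion on the arm-by-time contrast, not the time effect, and require it to hold under both age definitions. State how the two-month rate counts towards that conclusion.
- Reconcile the within-child-only statement in Section 2.3.2 with the inter-group factor in Statistical Methods.

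The cost is one more variable, a little more analysis, and possibly a smaller apparent acceleration.

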### 2.6. Sample Size Calculation and Statistical Analysis

Sample size calculation: The prevalence of cerebral palsy is 2.08 cases/1000 births. To obtain a good sample security, 30 subjects for each of the groups to be evaluated offer a confidence interval of 95% with a security of 10.

The initial GMFM and IMP score will be divided by the child’s months of age to calculate the rate of acquisition of their items so far. This calculation represents the mean distribution of the acquisition of these motor items. The acceleration values will be used to avoid errors in the assumption of how these items were acquired, since the tendency is to be exponential at these ages. The net values obtained in the valuation will not be considered, but the rate with which they have been obtained as a function of time will be. The rate of this development without intervention will be calculated at the time of the initial assessment, relative to the age of the patient. The proportion of the score necessary to obtain in the next two months to be able to accelerate that rate, instead of following the same previous trajectory, will be an unknown concept for all therapists and examiners.

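### The pre/post change in rate or acceleration of motor development cannot be attributed to therapy, and an age difference between the arms can carry the artefact into the group comparison

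*Protocol article*

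**What the plan says.** Section 4 of the Protocol article defines the GMFM rate before treatment as score over age, with a score of zero at birth: "The rate values are calculated by dividing the total score by the time (days of age) required to achieve it". Section 2.6 applies the same division to both scales (its sentence opens "The initial GMFM and IMP score will be divided by"), in months where section 4 uses days. For the treatment period, section 4 states: "Only new points acquired during this period were considered to calculate the rate of development and acceleration values in the intervention period". Acceleration is a difference of rates over elapsed time: "The acceleration factor is calculated by dividing the differences between final and initial rate (assumed to be zero at birth), by the age in days". Section 2.6 sets the raw scores aside: "The net values obtained in the valuation will not be considered".

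The article accepts that growth is not linear. Section 2.6 justifies using acceleration "since the tendency is to be exponential at these ages". Section 4 therefore adds an upper bound for the pre-treatment rate: "we performed a second rate calculation assuming that all the items were adquired during the last two months before the intervention". It expects the two calculations together to tell natural acceleration from a therapeutic change.

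The change is read within the child. Section 2.3.2 justifies not excluding earlier and concomitant treatment on the ground that each child is compared only with itself. Section 3 (Phase 3) says the short period lets changes be attributed to the therapy. Statistical Methods (section 3) also plans a repeated-measures ANOVA with time and treatment group as factors.

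**The concern.** A mean since birth and a two-month increment are different quantities. On a curve that bends upwards, the recent increment exceeds the lifetime mean; on one that flattens, it falls below. An untreated child would therefore appear to speed up or slow down according to age and curve shape. If that change is credited to therapy, either arm can show a benefit or a loss that is not there.

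The size of the artefact depends on age. Entry spans 0–36 months (section 2.3.1) and assignment follows therapist availability (sections 2.1 and 2.3), so an age difference between arms could pass it into the group comparison.

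The IMP raises a further problem. Section 2.4 says it also scores variability, adaptation, symmetry and fluency. These are not items accumulated from zero at birth.

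**Working it through.** **Inputs.** From the article: the definitions above, 2 months of follow-up, entry at 0–36 months, 30 per arm, 5% significance level. Growth curves, noise and age distributions are not given, so those below are assumptions. Therapy effect is zero unless stated.

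**Formulas.** For score S(t) at age t months and h = 2:
- pre rate = S(t)/t
- post rate = [S(t+h) − S(t)]/h
- bounding pre rate = S(t)/h

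**Untreated child at 12 months.** Quadratic example: pre 144k/12 = 12k; post (196k − 144k)/2 = 26k; bound 144k/2 = 72k.

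| Assumed curve | Pre | Post | Post/pre | Bound | Post/bound |
|---|---|---|---|---|---|
| Linear, kt | k | k | 1.00 | 6k | 0.17 |
| Quadratic, kt² | 12k | 26k | 2.17 | 72k | 0.36 |
| Exponential, e^(t/6) − 1 | 0.532 | 1.462 | 2.75 | 3.195 | 0.46 |
| Saturating, 1 − e^(−t/12) | 0.0527 | 0.0282 | 0.54 | 0.316 | 0.09 |

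A slower exponential (doubling every 12 months) gives 1.47. A logistic curve centred at 15 months gives 2.36 at 12 months and 0.48 at 24 months, so one curve can show gain or loss depending on age.

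**Bounding calculation.** Post exceeds the bound only if S(t+h) − S(t) > S(t): the child must gain more than the whole baseline score in two months. That is impossible once the baseline exceeds half the scale maximum. The bound does not always show slowing, however. For quadratic growth at 3 months, post is (25k − 9k)/2 = 8k, the bound is 9k/2 = 4.5k, and the ratio is 1.78.

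**Acceleration.** Pre acceleration is pre rate/t. If post acceleration is (post rate − pre rate)/h, quadratic growth at 12 months gives k before and (26k − 12k)/2 = 7k after, although true acceleration is constant. Linear growth gives k/12 before and 0 after. If instead the post period starts from a rate of zero, linear growth gives k/2 after, a 6-fold rise. The text allows either reading, and both mislead.

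**IMP.** An unchanged quality score S gives S/age before and, if the new-points rule is applied to it, 0 after.

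**Simulated false positives.** 2,000 trials of 30 per arm; ages uniform over 3–28 months; between-child lognormal SD 0.4; score error SD 1 point. Group-by-time was tested as a t-test on post minus pre.

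| Curve | Within-arm pre/post | Group×time, plain rate, equal ages | Same, one arm 6 months older | Group×time, bounding rate, 6 months older |
|---|---|---|---|---|
| Linear | 5% | 5.6% | 4.6% | 58% |
| Quadratic | 99% | 5.6% | 18% | 70% |
| Exponential (doubling in 12 months) | 88% | 4.9% | 28% | 69% |
| Saturating (12 months) | 100% | 5.0% | 6.6% | 36% |
| Logistic (centre 15 months) | 46% | 4.6% | 31% | 55% |

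With a 3-month imbalance, the plain rate gave 9–10% for the quadratic, exponential and logistic curves. Further runs under other assumptions reached 72% on the plain rate for convex curves and 76% on the bounding rate at 6 months. The 2-month score adjusted for baseline and age stayed at about 2–6.5% under the same imbalance.

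**Power for an assumed 2-point benefit, equal ages.** Bounding rate: about 5–7%, and 7–14% in another set of runs. Plain rate: 94–100%. Adjusted 2-month score: 98–100%.

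**The case against.** The strongest reply is that the trial has a concurrent control arm. Statistical Methods plans a time-by-group ANOVA, and both arms share the age and curve artefact, so the interaction removes it when ages are alike. This stands: false positives were about 5% on every curve with equal ages. A reader might infer that the rate outcome cannot reflect therapy at all. The documents do not support that, because a therapy effect adds new points and so enters the post rate directly; the plain rate kept good power.

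A reader might also infer that any age difference becomes a group effect. That too goes beyond the evidence. Under linear or saturating growth, a 6-month imbalance left the plain rate near 5%. The unadjusted raw gain is exposed to imbalance as well (14–19% on non-linear curves at 3 months), so adjustment matters as much as the choice of scale.

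The article is open that the second calculation is deliberately severe, more so for older children, and limits it to children older than two months at entry. It is therefore not undefined for younger infants. Section 4 also lists age among the factors whose influence will be considered.

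None of this rescues the within-child attribution. It also does not rescue the claim that two calculations can separate natural from therapeutic change. No age adjustment is attached to the stated ANOVA. An analysis plan not shown here might add one, but that would protect only the group comparison.

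**Conclusion.** The point holds in this form: within-child change in rate or acceleration is not evidence of a therapy effect under the non-linear growth the article itself expects. At 12 months the untreated post/pre ratio ranges from 0.54 to 2.75 over the assumed curves. The bounding calculation does not repair this, and its group comparison has almost no power.

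The group-by-time test on the plain rate is sound if the arms have similar ages, which the allocation method does not assure. With a 6-month imbalance its false-positive rate is about 18–72% for convex growth and near 5% for linear or saturating growth. Dividing IMP movement-quality scores by age is unfounded whatever the curve.

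The direction of these results follows from the stated definitions. Their sizes rest on assumed curves, noise and ages.

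**What to change.** 1. State that within-child change in rate or acceleration will not be read as a therapy effect, and amend sections 2.3.2, 3 (Phase 3) and 4 to match.
2. Base inference on the between-group difference in 2-month GMFM score, adjusted for baseline score and age in days and, where possible, GMFCS level. Gain per month with the same adjustment keeps the rate-of-development aim of sections 1.1 and 1.2. It gives the same treatment test when the interval is common to all children, and nearly so within the ±1 week window.
3. Analyse the IMP in the same way on its own scale.
4. Remove the sentence in section 2.6 that excludes net values.
5. Drop the acceleration and the second pre-treatment rate as evidence of effect, or keep them as description only.

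The cost is wording. Scores, assessment dates, age and GMFCS level are already collected, and section 4 reports complete data on only four subjects so far. Adjustment handles measured age and baseline score; it does not make allocation by availability random.

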#### 2.3.1. Inclusion Criteria

Male and female children between 0 and 36 months, with a risk of neurological alteration or diagnosis of cerebral palsy or neuromotor disease, who are admitted for assessment and/or treatment according to the Vojta therapy methodology or conventional treatment in the Physical and Rehabilitation Medicine Service will be included in this study. The diagnosis may be clinical and/or supported by the presence of lesions in complementary tests. Due to the fact that the diagnosis of cerebral palsy is confirmed in many cases after one year of life, the data of children in treatment for risk of neurological alteration will only be included retrospectively when said diagnosis has been confirmed. Younger children have not received a definite diagnosis of CP yet, but, based on the presence of lesions determined by magnetic resonance imaging, their risk of developing CP was estimated to be sufficiently high to justify their inclusion in the CP group. 

Parents or guardians must sign the informed consent that will allow us to use their data on therapeutic results, always in a pseudonymized (coded) way, guaranteeing confidentiality. 

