## 3. Methods and Timeline

Phase 1. Initial Assessment: Children who go to the rehabilitation center where they have been referred will be treated, an initial routine clinical examination will be performed, including: Personal/medical data collection.GMFM quantification.Treatment with the physiotherapist.Training of the parents in the home program.Recording for the IMP quantification.

Phase 2. Intervention period (2 months): The assignment to the therapist will be randomized according to the needs of the service, where each therapist will adapt the treatment according to the initial assessment. Both assessors and therapist cannot be blinded to the allocation or treatment, and both required live-direct performance. An external assessor (blind to both) will be able to score the IMP recordings. 

Children will receive weekly or fortnightly treatment, and their parents, family members, or carer will be trained in carrying out a home program. Each therapist will adapt the treatment according to the initial evaluation, as is usually performed in the rehabilitation service. During the treatment sessions, the physiotherapist will apply the therapy directly, either based on Vojta therapy or conventional physiotherapy. The frequency of repetition of the treatment at home and in the hospital will be recorded, depending on the availability of each family and the normal functioning of the service.

Phase 3. Second assessment at 2 months (±1 week, depending on follow up appointments).

Collection of data on the possible changes made in previous treatments and the frequency of home treatment (possible incidents due to illness or family limitations).GMFM quantification.Recording necessary for IMP quantification.

Children carried on clinically with the intervention, but this short period would allow us to attribute changes to RL, controlling better the influence of other factor (such as age maturation or other therapy inputs).

Study length. The data collection will be carried out for 4 years from the approval of the CEI. Only patients receiving healthcare with any of the therapies under investigation after authorization by the CEI will be included.

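### The starting rate for acceleration in the two-month period is not fixed, and under either reading the value cannot be compared with the pre-treatment one

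*Protocol article*

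**What the plan says.** Section 2.6 gives acceleration a protective role: "The acceleration values will be used to avoid errors in the assumption of how these items were acquired". Section 4 supplies the formulas. For the rate: "The rate values are calculated by dividing the total score by the time (days of age) required to achieve it", taking the newborn score as zero. For acceleration: "The acceleration factor is calculated by dividing the differences between final and initial rate (assumed to be zero at birth), by the age in days". For the treatment period: "The same rate and acceleration factors of acquisition are figured out between the initial assessment and after two months of the intervention", followed at once by the restriction "Only new points acquired during this period were considered to calculate the rate of development and acceleration values in the intervention period".

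Section 4 then adds a second pre-treatment calculation for children older than two months at the initial assessment. It places every point scored so far in the final two months before treatment, so that periods of equal length are compared. The article does not say which of the two pre-treatment calculations is primary. The Statistical Methods section plans a repeated-measures ANOVA with time (pre, post) and group as factors, and does not say which derived quantity enters it. Section 2.6 divides scores by months of age; Section 4 divides by days.

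**The concern.** Before treatment the starting rate is stated: zero at birth. For the treatment period it is not. Carrying the formula forward makes it the pre-treatment rate, which is built entirely from old points. Admitting only new points suggests a restart at zero. An analyst could defend either.

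Choosing one would not cure the problem. Each child contributes three points: an assumed zero at birth, the baseline score and the two-month score. Three points give one second difference, hence one acceleration. A separate pre-treatment value exists only because a zero rate at birth is also assumed, and it spans a period of different length from the post value. Acceleration is meant to protect against wrong assumptions about growth, so an apparent change in it could be read as a therapy effect when nothing in the child's course has altered.

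**Working it through.** **Inputs.** S = baseline score; A = age in days at baseline; N = new points over the T days of treatment. Score and rate at birth are zero (Section 4). Section 3 sets "Second assessment at 2 months (±1 week, depending on follow up appointments"; I take T = 61 days. Section 2.3.1 admits "Male and female children between 0 and 36 months". The article prints no acceleration figure, so there is none to reproduce.

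**Formulas.**
- Pre-treatment: (S/A − 0)/A = S/A².
- Post, carried-forward start: (N/T − S/A)/T.
- Post, start reset to zero: (N/T − 0)/T = N/T².

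**Check 1: constant rate r, true acceleration zero throughout.** S = rA and N = rT. Pre = r/A. Carried-forward post = (r − r)/T = 0. Reset post = r/T, so post/pre = A/T.

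| Age (days) | Carried-forward post | Reset post/pre |
|---|---|---|
| 30 | 0 | 30/61 = 0.5 |
| 61 | 0 | 1.0 |
| 183 (6 months) | 0 | 3.0 |
| 365 (12 months) | 0 | 6.0 |
| 730 (24 months) | 0 | 12.0 |

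With intervals of 67 to 53 days, the 12-month ratio runs from 365/67 = 5.4 to 365/53 = 6.9. If a 12-month-old's rate halves, the reset reading still gives 0.5 × 365/61 = 3.0 times the pre value, while the carried-forward reading is negative.

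**Check 2: constant true acceleration a from birth, correct ratio 1.** S = aA²/2 and N = a(AT + T²/2).
- Pre = a/2, already half the true value, because an average rate is treated as the rate at the end of the period.
- Carried-forward post = a(A + T)/(2T), so post/pre = A/T + 1: 4 at 6 months, 7 at 12 months.
- Reset post = a(A + T/2)/T, so post/pre = 2A/T + 1: 7 at 6 months, 13 at 12 months.

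**Check 3: the second pre-treatment calculation.** Pre = S/T².
- Reset: post/pre = N/S, identical to the ratio of the rates N/T and S/T, so acceleration adds nothing. For the constant-rate 12-month-old it is 61/365 = 0.17 (0.16 with T = 60), an apparent slowing.
- Carried forward from S/T: post = (N − S)/T², which exceeds S/T² only if N > 2S.

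**Check 4: between arms.** The pre-to-post change is N/T² − S/A² (reset) or N/T² − S/(AT) − S/A² (carried forward). The two differ by S/(AT), a baseline quantity. With arms balanced at baseline, the expected contrast under both is the between-arm difference in mean N, divided by T².

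Now suppose, purely as an illustration, that one arm is aged 183 days and the other 365, both with the same constant rate r. With the first pre-treatment calculation the spurious contrast is r(1/183 − 1/365) under either reading. Multiplied by 61, this equals the effect of a 0.17r difference in two-month rate, favouring the older arm. With the second calculation and the reset reading it is r(365 − 183)/61², equivalent to 2.98r, favouring the younger arm.

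**Check 5: a midpoint formula.** Take (N/T − S/A)/((A + T)/2), where the denominator is the time between the midpoints of the two periods. At constant rate it returns 0. At constant acceleration the numerator is a(A + T)/2, so it returns a exactly.

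**The case against.** The strongest defence is that a single consistent reading runs through Section 4: S/A² before, N/T² after and S/T² in the second calculation, with that last step added to guard against low averages over long pre-treatment periods. The zero rate at birth is declared openly. The hypothesis and main goal concern the rate, and the ANOVA is not tied to acceleration.

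Much of this stands, and it limits the point. A reader might infer that the article writes out two contradictory definitions. It does not: it gives one formula with an unstated starting rate. A reader might say that the unchanged child is scored as stopping. Zero acceleration means an unchanged rate, and zero is the true value; the fault is the fall from a positive pre value. The inflation is not universal either, since the reset ratio is about 1 at two months and lower in younger infants, who are eligible. Nor is the group comparison shown to be mostly age or unrelated to therapy: new points enter both post values, and Check 4 shows the same expected contrast under both readings when arms are balanced.

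What does not stand is that the consistent reading rescues the measure. It is the reset reading, which gives the unchanged 12-month-old a six-fold increase on one pre-treatment calculation and a fall to about one sixth on the other. The second calculation also leaves out children up to two months old.

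**Conclusion.** The point holds as an unfixed starting rate combined with a pre/post comparison that is invalid under either reading. For an unchanged acquisition rate, the within-child result is a fall to zero, or a ratio of age/61 reaching 12 at 24 months, or about 0.17 at 12 months against the second pre-treatment value. With truly constant acceleration, the two readings give 4 and 7 at 6 months and 7 and 13 at 12 months, where 1 is correct. These ratios rest on T = 61 days and idealised growth curves; r and a cancel.

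The within-child change thus depends strongly on age and on the reading. Bias between arms needs a baseline difference in age or score. The article does not show one, but allocation by therapist availability (Sections 2.1 and 2.3) does not rule it out.

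**What to change.** Delete the separate pre-treatment acceleration and the pre/post acceleration comparison. Then do one of the following:
- drop acceleration and analyse the rate; or
- compute one value per child, (two-month rate − pre-treatment rate) / ((age at baseline + days between assessments)/2), and compare it between arms with adjustment for age at baseline.

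Use actual days in every denominator, so that Sections 2.6 and 4 agree. State which pre-treatment rate calculation is primary and which is a sensitivity analysis.

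No new data are needed. The cost is a within-child pre/post acceleration result, which three points per child cannot support without the assumed zero rate at birth. Section 4 reports complete assessments for four subjects and no results yet, so the definition can still be settled before outcomes are analysed.
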